### Part B

The experimental aspirin regimen associated with a significantly lower serum TXB_2_ level and non-inferior urinary PGIM excretion rate (i.e., ≤30% reduction) as compared to aspirin 100 mg od, will be selected for part B, and patients will be randomized in an open-label fashion to the standard vs. the optimized multiple dosing regimen for 20 months. The primary end point of part B will assess the long-term persistence of the superior biochemical efficacy of the optimized vs. standard aspirin regimen, in at least 6 out of 10 determinations of serum TXB_2_ that will be performed over 20 months. Secondary end points of part B will explore the following: (i) the safety of the experimental aspirin regimen, as reflected by any major bleeding and gastrointestinal symptoms considered attributable to aspirin; (ii) effectiveness in reducing MPN-specific symptom burden and pain attributable to microcirculatory disturbances; and (iii) stability over 20 months of the degree of platelet activation in vivo, as assessed by urinary TXM. The stability of TXM will be assessed in a subgroup of 150 patients.

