## Study end points and statistical analysis

The co-primary end points of part A are as follows: (1) platelet TXA_2_ production ex vivo, as reflected by serum TXB_2_, measured in samples collected in the morning, before the next aspirin intake; and (2) vascular PGI_2_ biosynthesis in vivo, as reflected by urinary PGIM excretion in a urine sample collected in the morning before the next aspirin intake. Urinary TXM excretion represents a secondary end point. These biomarkers will be measured at randomization and at 14 ± 2 days thereafter.

The primary end point of part B is represented by serum TXB_2_ measured 10 times in samples collected in the morning, before the next aspirin intake. The secondary end points are related to exploratory assessment of safety and tolerability of the experimental aspirin dosing regimen, and stability over time of in vivo platelet activation, as detailed above.

Based on previous findings^12,14^, we expect the mean ± standard deviation (SD) serum TXB_2_ in ET patients on aspirin 100 mg od and 100 mg bid to be 22 ± 33 and 5.0 ± 6.0 ng/ml, respectively. We plan to test with *α*-error of 0.05 and a *β*-error of 0.2 (power 80%) the following hypotheses:100 mg bid is superior to 100 mg od, with a ≥50% reduction in serum TXB_2_ (required sample size 70 patients/arm)100 mg tid is superior to 100 mg bid, with a ≥50% reduction in serum TXB_2_ (required sample size 70 patients/arm)

Anticipating a 30% dropout over the entire study duration, we plan to enroll 100 patients/arm to ensure adequate statistical power. For urinary PGIM, we expect the mean ± SD PGIM excretion rate in ET patients on aspirin 100 mg od to be 195 ± 119 pg/mg creatinine^33^. Using the above sample size (*n* = 70 patients/arm), the study has 80% power to test the hypothesis that any experimental treatment may reduce urinary PGIM to <140 pg/mg creatinine, i.e., by >30%. This threshold of PGIM inhibition vs. the standard dosing regimen can be considered reasonably safe based on the following considerations: urinary PGIM excretion is minimally affected by low-dose aspirin in healthy subjects^32,33^; in ET subjects, aspirin 100 mg bid did not significantly modify PGIM as compared to 100 mg od^33^; and this threshold corresponds to the intra-subject coefficient of variation on repeated measurements of PGIM excretion over time^39^.

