The same 300 ET patients will be randomized in part B of the study that will test the long-term persistence of superior biochemical efficacy of the optimized vs. standard dosing regimen. In all, 112 patients/arm will be needed to assess with an *α*-error of 0.05 and 80% power, a reduction of at least 50% in serum TXB_2_ with the optimized regimen (100 mg bid or tid) vs. the standard aspirin regimen (100 mg od), in at least 6 out of 10 determinations performed over 20 months.

Differences in mean serum TXB_2_ values will be evaluated by one-way analysis of variance, using Scheffe multiple-comparison test to allow comparisons of the three different treatments in part A. Analysis of covariance using multiple regression with dummies for the different treatments will be used if, at single univariate analysis, major differences (*p* < 0.05) in the distribution of gender, age, platelet count, JAK2 mutational status, spleen size, aspartate aminotransferase, alanine aminotransferase, or creatinine, and type of cytoreductive drug (if any) will be present between the three treatment subgroups. Both intention-to-treat and per-protocol analyses will be carried out.

It can be reasonably anticipated that a portion of the ET patients recruited in this trial according to the 2008 WHO diagnostic criteria^4^ might fall into the category of the pre-PMF according to the revised 2016 WHO criteria^38^. In a large international study of 1104 ET patients, diagnosis was revised to pre-PMF in 16%;^40^ these patients have been reported having an increased tendency toward bleeding^41^. Therefore, we will perform a pre-specified secondary analysis in the group of patients who will develop major and/or non-major clinically relevant bleeding in comparison with the patients with an uneventful course. All the bone marrow biopsies of the recruited patients will be revised by an ad hoc committee formed by the pathologist of the Coordinating Center and the pathologist of the Center where the patient had been recruited in order to assess whether patients had a true-ET or a pre-PMF according to the revised WHO classification;^38^ both the pathologists involved in the bone marrow revision will be blinded to the clinical characteristics of the patients. If the pathologists will provide different opinions, we will consult with a qualified third pathologist. The incidence of pre-PMF in patients with bleeding events will be compared to that found in non-bleeders.

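### Part A is sized at 70 per arm with an unadjusted 0.05 but tested with Scheffe, so the stated 80% power for bid versus od at a 50% reduction is not delivered at that size

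*Protocol article*

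**What the plan says.** All references are to the protocol article.

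- **Sizing** (Study end points and statistical analysis). Part A is planned as follows: "We plan to test with *α*-error of 0.05 and a *β*-error of 0.2 (power 80%) the following hypotheses". The first hypothesis is "100 mg bid is superior to 100 mg od, with a ≥50% reduction in serum TXB_2_ (required sample size 70 patients/arm"); the second is "100 mg tid is superior to 100 mg bid, with a ≥50% reduction in serum TXB_2_ (required sample size 70 patients/arm"). The expected serum TXB2 values are given for "100 mg od and 100 mg bid to be 22 ± 33 and 5.0 ± 6.0 ng/ml, respectively". No SD is given for tid. Neither the sidedness of the 0.05 nor any allowance for several comparisons is mentioned.
- **Enrolment** (same section). "Anticipating a 30% dropout over the entire study duration, we plan to enroll 100 patients/arm to ensure adequate statistical power". Part A is read at 14 ± 2 days.
- **Analysis** (same section). Mean serum TXB2 is compared by one-way ANOVA, "using Scheffe multiple-comparison test to allow comparisons of the three different treatments in part A".
- **Selection** (Part B). The regimen taken forward is described as "The experimental aspirin regimen associated with a significantly lower serum TXB_2_ level" than aspirin od, together with non-inferior PGIM. No significance level or test is named there.

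**The concern.** Scheffe's procedure spreads its 5% error over every possible contrast among the three arms, so each pairwise comparison faces a stricter threshold than 0.05. If the sample size was computed at 0.05 per comparison, the power quoted belongs to a different test from the one that will be run.

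Bid versus od is one of the two contrasts that can admit a regimen to the 20-month part B. If its power is materially below 80%, a regimen that achieves the minimum reduction of interest is more likely to be missed than the plan says. The selection rule is also not linked to a test or level, so a reader cannot tell from the article which threshold a regimen must meet.

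**Working it through.** **Inputs.** From the article: od mean 22, SD 33; bid mean 5.0, SD 6.0; reduction to detect 50%, so 22 to 11 ng/ml (difference 11); alpha 0.05; power 80%; 70 per arm evaluable, 100 per arm enrolled; three arms. Assumed here, because the article does not give them: the tid SD, and a bid SD of 16.5 as an alternative to 6.0 (the SD halving along with the mean).

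**1. Reproduce 70 per arm.** n = (z_α + z_β)² (s₁² + s₂²) / d².

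- One-sided 0.05, SDs 33 and 16.5: (1.645 + 0.842)² × (1089 + 272.25) / 121 = 6.18 × 11.25 = 69.6, so 70. Exact match.
- Two-sided 0.05, SDs 33 and 6: (1.960 + 0.842)² × (1089 + 36) / 121 = 7.85 × 9.30 = 73. At 70 per arm, SE = √(1125/70) = 4.009, 11/4.009 = 2.744, and power = Φ(2.744 − 1.960) = 78%. Near match.
- Tid versus bid, one-sided 0.05, SDs 6 and 6, difference 2.5: 6.18 × 72 / 6.25 = 71.2, so 72. Near match; two-sided gives 91.

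Every reading that fits uses an unadjusted 0.05.

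**2. Scheffe threshold.** Critical |t| = √(2 × F(0.95; 2, 207)) = √(2 × 3.0395) = 2.466, a two-sided per-pair p of 0.0145.

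**3. Power for bid versus od under Scheffe, difference 11.**

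- Pair-specific SE: power = Φ(11/SE − 2.466), with SE = √((s₁² + s₂²)/n).
- Pooled ANOVA error: the difference must exceed 2.466 × √(2·MSE/n), with MSE the mean of the three variances, while its true SE is still √((s₁² + s₂²)/n).

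For example, with SDs 33/6/6, MSE = (1089 + 36 + 36)/3 = 387. The critical difference is 2.466 × √(774/70) = 8.20, and power = Φ((11 − 8.20)/4.009) = 76%.

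At 100 per arm the critical |t| is 2.460.

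| SDs od/bid/tid | Standard error | Power, 70/arm | Power, 100/arm |
|---|---|---|---|
| 33/6 | pair | 61% | 79% |
| 33/6/6 | pooled | 76% | 89% |
| 33/16.5 | pair | 51% | 70% |
| 33/16.5/8.25 | pooled | 67% | 82% |

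Simulation with normal data agrees to within a percentage point.

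**4. How much of the loss is Scheffe.** With the pair SE at 70 per arm, power at two-sided 0.05 is 78% (33/6) and 70% (33/16.5). Scheffe therefore costs about 17 and 19 points. In the second case the remaining 10 points below 80% come from moving from a one-sided to a two-sided test.

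**5. At the expected means.** Difference 17, SDs 33 and 6, 70 per arm: 17/4.009 = 4.241, and Φ(4.241 − 2.466) = 96%. Pooled error gives 98% to 99%.

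**6. Sensitivity to shape.** The figures above use the normal-theory basis that yields 70. For log-normal data with the same means and SDs, tested on the raw scale at 70 per arm, simulation gives Scheffe power of 64% and 78% (33/16.5/8.25, pair and pooled SE) and 81% and 93% (33/6/6). Power at two-sided 0.05 in the same runs is 82% to 98%, so Scheffe still costs power.

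**7. What a less strict procedure would do.** Take a closed three-arm test (overall F, then each pair at two-sided 0.05) with pooled error. Set SDs 33/16.5/8.25, od and bid means equal at 22, and tid at 5.5. MSE = (1089 + 272.25 + 68.06)/3 = 476.4 and the pooled SE is √(952.9/70) = 3.69, against a true SE of √(1361.25/70) = 4.41. The pair test rejects at about 1.97 × 3.69 = 7.27, which is only 1.65 true standard errors. The od-versus-bid false-positive rate is about 10% in simulation, against about 4% for Scheffe.

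**The case against.** **Seventy is not the expected part A sample.** The 30% dropout covers the whole study, including 20 months of part B, and part A is read at two weeks. This stands: near 100 per arm, Scheffe power is about 70% to 89%.

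**The shortfall is only at the minimum effect.** This also stands: at the means the article expects, power is at least 96%.

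**Scheffe is valid and pre-specified, and 0.05 may be its family-wise level.** True, but the quoted power is then wrong, because 70 per arm does not give 80% on that reading under the assumptions that reproduce it.

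**The missing link may be in the full protocol.** Sidedness may well be stated there. The mismatch between the sizing and the named test is visible in the article itself.

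Three stronger readings are tempting, and the documents do not support them:

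- *That a result with p between 0.0145 and 0.05 passes one decision rule and fails another.* The 0.05 is a sizing input, and Scheffe is the only part A test named. There is one rule, with its link to the selection step left unstated.
- *That power is 67%.* That figure needs a bid SD of 16.5 and a tid SD of 8.25. The article gives 6.0 for bid and nothing for tid. Setting it against a one-sided, unpooled 80% also mixes sidedness and error terms.
- *That Scheffe's strictness buys nothing.* With the unequal SDs this trial expects and a pooled error, its margin is what keeps the od-versus-bid error rate near 4% instead of about 10%.

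**Conclusion.** The point holds in a limited form. The 80% power at 70 per arm rests on an unadjusted 0.05, while the named test works at about 0.0145 per pair. At the minimum 50% reduction with 70 evaluable patients per arm, power for bid versus od is about 51% to 76% under normal-theory assumptions. The spread comes from the bid SD (6.0 or 16.5), the assumed tid SD, and a pooled or pair-specific error. Skewed data could raise these figures, in some cases above 80%, but the gap between the sizing test and the named test remains.

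The practical risk is moderate: most of the 100 per arm should reach the two-week reading, and the expected effect is well above the minimum. This is a power statement and a selection criterion to correct. It does not show that the trial is too small for the effect it expects.

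**What to change.** 1. In Study end points and statistical analysis, state whether tests are one- or two-sided and that 0.05 is the family-wise level for part A.
2. Restate the power at 70 per arm (and, usefully, at the number expected at two weeks) on the criterion actually used, giving the SDs assumed for all three arms and the error term.
3. In Part B, state that the significance condition in the selection rule means significance under the part A procedure.

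Replacing Scheffe is optional. If a closed three-arm test (overall test, then each pair at two-sided 0.05) is adopted to recover power, both steps should use an unequal-variance (Welch) or log-scale analysis, because the pooled version does not hold its error rate with SDs this unequal. Its power must then be computed afresh for that version; power figures from a pooled closed test should not be carried over.

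The cost is a few sentences and one recalculated power figure, with no additional patients, samples or visits.

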### Part A

Patients will be randomized (1:1:1) in a double-blind fashion to aspirin 100 mg od (standard of care), 100 mg bid (i.e. breakfast and dinner), or 100 mg tid (i.e., breakfast, lunch, and dinner). Matching placebo will be used so that all patients will take active drug and placebo tablets tid. At randomization and after 2 weeks of study treatment, patients will undergo blood and urine sampling for serum TXB_2_ and urinary PGIM and TXM measurements at 8 a.m., immediately before aspirin dosing; thereafter, they will resume their open-label, standard aspirin regimen for the time interval necessary to assay serum and urine samples and analyze the data. The primary end points of part A will assess the biochemical efficacy, as reflected by the degree of suppression of serum TXB_2_ throughout the dosing interval, and biochemical safety, as assessed by urinary PGIM excretion, of the two experimental dosing regimens as compared to the standard regimen of aspirin administration. The secondary end point will assess their impact on in vivo platelet activation, as reflected by the urinary excretion of TXM.

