## Study population and patient eligibility

Three-hundred ET patients will be enrolled by 11 Italian hematological centers. Both patients with newly diagnosed and previously diagnosed disease were eligible. Inclusion and exclusion criteria are listed in Table 1. The following characteristics will be recorded at study entry: age at diagnosis; history of thrombosis or major bleeding; mutational profile (i.e., JAK2, CALR, and MPL mutations); blood count; spleen size; constitutional symptoms; and cytoreductive agents. Of note, the study was designed and approved by the AIFA and Ethic Committees before the publication of the revised 2016 WHO classification for tumors of the hematopoietic and lymphoid tissues^38^, therefore the inclusion criteria reflect the WHO classification at the time of study approvals.

**Table 1 Tab1:** Inclusion and exclusion criteria

Main inclusion criteria	Main exclusion criteria
*All of the following*: Age between 18 and 75 years A WHO 2008-defined ET diagnosis Ongoing aspirin 100 mg daily since at least 3 months, according to the judgment of the referring hematologist The patient understands and voluntarily signs an informed consent	*Any of the following*: Platelet count > 1 000 000/μl on three occasions over the 2 months before enrollment Diabetes according to American Diabetes Association criteria Creatinine level > 1.5× upper limit of normal Liver disease defined as AST and/or ALT values > 3× upper limit of normal Active gastrointestinal disease Obesity (BMI > 30 kg/m^2^) Smoking habits (>5 cigarettes/day) History of major bleeding History of cancer in the previous 3 years, except for treated early-stage squamous or basal cell skin carcinomas Pregnancy or lactation Use of nonsteroidal anti-inflammatory drugs >3 times/week Use of antiplatelet agents other than aspirin 100 mg Use of oral anticoagulants including anti-vitamin K, anti-Xa, or -IIa agents Use of heparins or fondaparinux Chronic use of steroids (prednisone > 5 mg/day or equivalent)

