In order for the serum TXB_2_ assay to reflect the maximal biosynthetic capacity of blood platelets and its blockade by COX-1 inhibitors in a reproducible fashion, initiation of whole-blood clotting at 37 °C must rapidly follow peripheral blood sampling. However, a reproducible implementation of this procedure in multicenter studies might face practical hurdles, such as logistic delays between blood withdrawal from patients and access to a thermostatic bath, as well as the lack of appreciation of the time- and temperature-dependence of TXB_2_ production during blood clotting. Consistent with this expectation, a comparison of serum TXB_2_ values in two large, multicenter cohorts of aspirin-treated patients^45,46^ showed up to 10-fold difference in median TXB_2_ levels (7 and 0.6 ng/ml in the ADRIE^46^ and BOSTON^45^ studies, respectively) that could not be explained by patient characteristics or analytical biases^47^. Two recent in vitro studies showed that even a minor delay in starting 37 °C incubation can time-dependently underestimate serum TXB_2_ levels^17,48^, and thus potentially account for variable aspirin responsiveness across studies and centers. Thus, we assessed the feasibility of obtaining reliable serum TXB_2_ measurements across the ARES study centers. All participating investigators were given a detailed operative manual for the pre-analytical procedures, and all centers were supplied with the same disposable material for collecting and processing blood. Each center recruited five healthy, non-smoker subjects not being treated with any medication, and with normal hematochemistry, who did not take any NSAID or aspirin in the previous 10 days. The reason for including healthy, aspirin-naive subjects were as follows: the high absolute values of serum TXB_2_; the lack of influence of pharmacological interventions; and the possibility of detecting even small differences in absolute serum TXB_2_ values. The study was conducted in accordance with the Declaration of Helsinki and received ethics committee’s approvals in all participating centers.

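### Part A serum TXB2: covariate adjustment is switched on by baseline significance tests and leaves out baseline TXB2, so chance picks the model and precision is lost

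*Protocol article*

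**What the plan says.** All references are to the protocol article.

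- **Test.** The section on study end points and statistical analysis fixes the part A comparison: "Differences in mean serum TXB_2_ values will be evaluated by one-way analysis of variance, using Scheffe multiple-comparison test". The sentence names serum TXB2 only.
- **Trigger.** The next sentence reads "Analysis of covariance using multiple regression with dummies for the different treatments will be used if, at single univariate analysis, major differences", with the threshold set at p<0.05. The tests compare all three arms and look for a difference "in the distribution of gender, age, platelet count, JAK2 mutational status, spleen size, aspartate aminotransferase, alanine aminotransferase, or creatinine, and type of cytoreductive drug". That makes nine candidates: gender, age, platelet count, JAK2 status, spleen size, AST, ALT, creatinine and type of cytoreductive drug. Baseline TXB2 is not among them.
- **Baseline data.** The same section says of TXB2, PGIM and TXM: "These biomarkers will be measured at randomization and at 14 ± 2 days thereafter". The Part A section has both samples drawn at 8 a.m., immediately before dosing.
- **Treatment at baseline.** Table 1 requires "Ongoing aspirin 100 mg daily since at least 3 months". The design section adds a run-in of 7–10 days to synchronise the time of intake.
- **Allocation.** "Patients will be randomized (1:1:1) in a double-blind fashion" (Part A section).

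**The concern.** In a randomised comparison, any baseline difference between arms is a chance finding. A p-value for that difference measures how unlucky the allocation was, not whether the variable predicts the outcome. A rule that adjusts only when p<0.05 can therefore bring in a variable with no bearing on TXB2 and leave out a prognostic one that happens to be balanced. The analysis model is then unknown until the data are seen.

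The omission of baseline TXB2 compounds this. Each patient's baseline sample is that patient's own TXB2 on the control regimen, taken under the same pre-dose conditions as the day-14 sample. No analysis in the article uses it. At stake is the precision of the TXB2 comparison that helps decide which regimen goes into part B.

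**Working it through.** **1. The plan's own sample size.** The article gives 70 per arm for a 50% reduction, with α 0.05 and 80% power. From an od mean of 22 ng/ml the difference is 11. With SD 33 on od, an SD of 16.5 in the comparator (halved with the mean, an assumption) and one-sided α:

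n = (33² + 16.5²) × ((1.645 + 0.842)/11)² = 69.6, so 70 per arm.

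70/0.70 = 100, the stated enrolment per arm. The figure reproduces, and it takes no credit for covariate adjustment.

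**2. How often chance alone triggers the switch.** Nine tests at 5%, all nulls true by randomisation, taken as independent:

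1 − 0.95⁹ = 0.370.

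In simulation with two of the nine (AST and ALT) correlated, the rate was 35.5% to 36.5%.

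**3. What the trigger achieves.** The simulation had 3 arms of 70 and 4,000 runs per setting. The outcome was normal with equal variances, and among the nine covariates only platelet count was related to it. Tests were two-sided at 5% on one contrast without the Scheffé correction, with an effect that gives plain ANOVA about 80% power.

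| Baseline to day-14 correlation (assumed) | Power: ANOVA | Power: conditional rule | Power: ANCOVA with baseline |
|---|---|---|---|
| 0.5 | 80.0% | 79.5% | 90.0% |
| 0.7 | 79.7% | 79.8% | 97.2% |

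Under no effect, rejection rates were 4.6% to 5.3% across all three methods. The conditional rule gains practically nothing, and it does no visible harm to type I error.

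**4. Size of the gain for TXB2.** Adjusting for baseline multiplies the residual variance by 1 − ρ². The documents do not give ρ, so a range is shown.

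| ρ (assumed) | 1 − ρ² | Variance reduction | Patients per arm giving the information of 70 unadjusted |
|---|---|---|---|
| 0.3 | 0.91 | 9% | 64 |
| 0.5 | 0.75 | 25% | 53 |
| 0.7 | 0.51 | 49% | 36 |

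These factors assume a linear relation and a common variance. The article expects "100 mg od and 100 mg bid to be 22 ± 33 and 5.0 ± 6.0 ng/ml, respectively". On od the SD exceeds the mean, which for a quantity that cannot be negative implies strong skew. The SD also falls from 33 to 6 on bid. On the raw scale, and in the bid and tid arms, the gain may therefore be smaller.

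**5. PGIM, as an indication only.** The article gives 195 ± 119 pg/mg creatinine (CV 119/195 = 0.61) and says the 30% threshold corresponds to the intra-subject CV. If that CV holds in these patients (an assumption), the log-scale variances are:

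- total: ln(1 + 0.61²) = 0.317
- within-subject: ln(1 + 0.30²) = 0.086

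The implied correlation is 1 − 0.086/0.317 = 0.73 and the variance factor 1 − 0.73² = 0.47, a reduction of about half.

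**The case against.** **TXB2 power may already be ample.** On the expected values, od against bid differs by 17 with SE √((33² + 6²)/70) = 4.01. Then 17/4.01 − 1.96 = 2.28, or about 99% unadjusted power at two-sided 5% (normal approximation, no multiplicity correction). This stands: if those values are right, lost precision is unlikely to change that comparison. It does not cover tid against bid, where a difference of 2.5 with SD 6 in both arms gives 69% two-sided or 79% one-sided at 70 per arm. That is also where the gain from baseline is least certain.

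**Baseline TXB2 as the strongest predictor is not documented.** That is correct. The case rests on the sampling design and on an assumed range of correlations.

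**Type I error.** A reader might infer that a data-dependent model makes the p-values misleading. The simulation does not support this: rejection under the null stayed near 5%.

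**PGIM.** A reader might infer that the plan discards baseline PGIM too. The ANOVA sentence covers TXB2 only and no PGIM model is stated, so silence in a condensed article is not a finding. A large gain in non-inferiority power can be computed: 75% to 97% on the log scale with margin 0.70. It needs a true 10% fall, one-sided 2.5%, 70 per arm and the transferred CV. Changing one input at a time, unadjusted power is 96% with no true fall, 84% at one-sided 5%, and about 88% at 100 per arm. The article does not fix these inputs.

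**Centre.** The assay section warns that delayed incubation may "potentially account for variable aspirin responsiveness across studies and centers", and 3 of 11 centres were out of range at first. They changed their procedure before enrolment, and the repeat values were in range. A residual centre effect in the trial is not shown.

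**Conclusion.** The point holds for part A serum TXB2. The article itself states the test, the covariate list and the p<0.05 trigger, so this is a stated rule and not a gap left to an analysis plan. The rule would change the model by chance in about 37% of properly randomised trials if the nine tests are independent. It also leaves out a baseline value that is already measured under matching conditions.

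The consequence is avoidable imprecision and a model chosen by chance. Residual variance is larger than it need be, and baseline adjustment would cut it by about 9% to 49% for assumed correlations of 0.3 to 0.7, possibly less on the raw scale or in the multiple-dose arms. The documents do not support reading this as material type I error inflation, as a fault in a stated PGIM analysis, or as evidence of uncorrected centre effects. It is an improvement that should be made, not a threat to the trial's validity.

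**What to change.** Delete the p<0.05 trigger. Prespecify one primary ANCOVA for part A serum TXB2, fitted to all patients in the analysis set, with treatment and baseline TXB2. Log-transform both TXB2 values by preference, given the skew. Add any prognostic covariates chosen in advance (for example platelet count or cytoreductive drug) and keep them whatever the baseline table shows. Centre is optional.

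For PGIM, consider stating the same baseline-adjusted approach when its analysis is written down.

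No new data are needed: baseline TXB2 and the listed characteristics are already to be recorded. The cost is a change of wording to a primary analysis, which may need a protocol amendment because the design has regulatory and ethics approval. It should be settled before unblinded part A data are examined.
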